## Abstract

Supplemental Digital Content is available in the text

## Background

1

Telangiectasias are defined as abnormally dilated venules (or capillaries) in the intradermic portion of the skin, with reddish or bluish tinge, their diameter not exceeding 1 mm.^[1]^ Usually they do not cause clinical symptoms, but rather complaints about cosmetic; some patients, however, report some pain, itching, cramping or heaviness at the site.^[1]^ They have been classified by the American Venous Forum as mild venous disease C1 CEAP (clinical, etiologic, anatomic, and pathophysiologic classification—CEAP), along with the reticular veins, where no varicose veins are found.^[2,3]^

Treatment of telangiectasia is supported by some researchers as the factor of clinical and cosmetic improvement for patients.^[1,4,5]^ The techniques that have been most widely used are those promoting sclerosis of the target veins, using sclerosing intravenous solutions or transdermal laser.^[6]^ The use of laser promotes the elimination of telangiectasia by selective transdermal photothermolysis, obliterating the vessel with a heat-induced injury provoked by a specific light length;^[6]^ chemical sclerotherapy uses a variety of chemical agents that primarily promote irritation, dehydration, and destruction of the endothelial cells, resulting in elimination of the vein.^[7]^ There is no evidence, however, of more efficacy when comparing the chemical techniques to laser therapy.^[8]^ Chemical sclerotherapy is the most widely used method due to its technical simplicity, rapid return to daily activities, and low cost. It is usually well tolerated by patients since it is almost painless, requiring no anesthesia, the discomfort being related to the venipuncture and drug infusion.^[7,9]^ All sclerosing agents available on the market have been reported as effective in the treatment of cosmetic venous disease, the choice being guided by the preference and experience of the attending physician.

Hypertonic glucose is a potent hyperosmolar sclerosing solution that promotes dehydration and destruction of endothelial cells and obliteration of the vessel lumen. Polidocanol is a detergent that acts by destroying the vein wall lipids and the intercellular “cement,” what causes endothelial maceration and obliterates the vessel.

Some papers point out that the sclerosing power of polidocanol and sodium tetradecyl sulfate (STS) would be higher than hyperosmolar agents;^[10–12]^ however, both are more fluid and can flow to unwanted vessels. Those opposed to the use of polidocanol, warn against adverse effects such as tissue necrosis, allergic reactions, anaphylaxis, increased risk of deep venous thrombosis (DVT), pulmonary embolism (PE), scotoma, and gas embolization (when used in foam form).^[13]^ These events are rare and often related to miscalculated doses.^[14,15]^ Some minor adverse events such as hyperpigmented spots, as well as mild systemic adverse events such as coughing, brief scotoma, light lipothymia, are described as being more often associated with the use of polidocanol.^[16]^ On the other hand, other authors believe that the side effects can be avoided if the volume and infusion time are well calculated, therefore rendering better results without a higher rate of adverse events.^[17]^

A commercial presentation of polidocanol 0.2% diluted in glucose 70% has been used in Brazil with apparent success and safety but with no scientific proof. In a pilot study of this institution, there was a trend toward better results with the use of this solution, justifying, therefore, what we intend to test in this study, comparing the solution of polidocanol 0.2% diluted in glucose 70% to glucose 75% solution for the treatment of lower limbs telangiectasia.

The hypothesis to be tested is that the polidocanol 0.2% diluted in glucose 70% is more efficient than glucose 75% in eliminating lower limbs telangiectasia (efficacy). Differences in safety will also be investigated (minor and major adverse events).

## Methods/design

2

### Study design

2.1

Single-center, prospective, randomized, triple-blind study to compare the efficacy in promoting the disappearance of telangiectasia in a treated lower extremity comparing photos taken before treatment and 60 days post-treatment. Two commonly used sclerosing solutions (polidocanol 0.2% diluted in glucose 70%, and glucose 75% solution) will be used and compared. Safety of the solutions will also be investigated, evaluating any major (DVT and skin necrosis) and minor adverse events (hyperpigmented spots, small ulcers and edema at the site of the application). The sample size was statistically estimated as 96 treated limbs (see Statistical analysis).

### Ethics approval and consent to participate

2.2

This study will be conducted in accordance to the principles of the Declaration of Helsinki, ISO14155, Data Protection Act, and guidelines for Good Clinical Practice. The Research Ethics Committee (REC) of the Botucatu Medical School, UNESP, São Paulo, Brazil, has approved this study, which was registered under the number 4127–2012 (see REC, supplemental digital content 1). During the screening visit, all patients will be fully informed of the benefits and risks of the study and the principal investigator will obtain the signature of the free and informed consent form (ICF) for all participants, before enrollment (see ICF, supplemental digital content 2). The subjects may leave this study at any point in time without any constraint, whenever they will.

All data will be sent to the ethics committee in the end of the study or if occur any major adverse effect. As the study provides a unique intervention, you can not interrupt the treatment.

The ClinicalTrials.gov identifier for this study is NCT02657252, obtained on January 12, 2016 (Acronym PG3T).

### Selection, inclusion, randomization, and masking

2.3

The sample will be of convenience, starting with a random and temporal list of patients who wish to do aesthetic treatment with sclerotherapy in the lower extremities due to mild venous disease - CEAP C1, in our institution. The patients will be invited by telephone to participate in the study, following the order of established by consulting the electronic database of our institution. They will be invited to attend a scheduled outpatient visit for clinical evaluation, and in order to be informed about the working methods. In this screening evaluation, patients who present telangiectasia on the lateral side of the thigh will then be invited to participate in the study and sign the ICF.

The inclusion will be random, using a spreadsheet electronically generated by the web-based free-access computer program Stat Trek (http://stattrek.com/Tables/Random.aspx). The patients will be randomized in 2 groups; one will receive treatment with 0.2% polidocanol diluted in glucose 70%; the other will be treated with glucose 75%. A trained nurse will generate and store all data in an opaque envelope for the entire duration of the study and prepare the solutions that will be used in the treatments, with sequential allocation in accordance with the order of addition. The solutions will be prepared in a medication room (different from the treatment room); the product (5 mL) will be drawn a sterile syringe identified only with the patient's protocol number, a few minutes before use, in such a way that the physician who will perform the procedure will have no contact with this phase of the research. It is noteworthy that the 2 drugs are colorless and odorless, with similar viscosity, what will promote an efficient blinding. Thus, all study participants will be blinded, patients, care providers, outcome assessors, and data analysts (triple blinded).

### Eligibility criteria

2.4

The inclusion and exclusion criteria are depicted in Table 1.

**Table 1 T1:**
[figure not shown]
Eligibility criteria.

### Pretreatment details

2.5

The patients will be included if they present telangiectasia not related to varicose veins on the side of the thigh of one of the lower extremities. The clinical diagnosis will be confirmed before treatment by duplex ultrasonography. Clinical data such as comorbidities, demographics and other relevant information will be compiled in specific forms for further analysis. All patients who do not meet the inclusion criteria during the screening evaluation will be referred to the routine outpatient clinic.

### Treatment area

2.6

The treatment area was defined as the lateral thigh of a lower limb (limited to 1 member per patient, independent of the side) and the target area is a rectangle 15 cm long and 10 cm wide, generating a 150 cm^2^ treatment area. For better reproducibility of the results, a template was made of cloth with velcro fixation to be positioned on the line of the knee joint. The open rectangular area will therefore be positioned 5 cm above the knee joint and the lower and anterior vertex of the rectangle will be positioned on the lateral aspect of the patella (Fig. 1). In order to facilitate the analysis of the pictures, a plastic ruler will be displayed at the edges of the template. After photographing the target area, small dots of permanent marker will be made in order to define the target area; the template will then be removed to facilitate the treatment. Telangiectasias that cross the edges of the template will also be entirely treated, so that small variations in the position of the template will not cause difficulties for the analysis of the results.

**Figure 1 F1:**
[figure not shown]
Schematic representation of the treatment area in this study.

### Photographic record

2.7

Photos of the patients will be taken in order to register the 3 stages of the research: one before the treatment (D0), one 7 days after treatment (D7), and the last 60 days after treatment (D60). A high definition camera will be used to take all the pictures (D7000 Nikon Lens™: AF-S Nikkor 18–105 mm ™ 1: 3.5–5.6G). In order to avoid possible bias, comparisons will always be conducted on the same patient through photographic analysis before and after treatment, to establish disappearance of telangiectasias on the treated area (see “Outcomes”), as well as the occurrence of hyperpigmented spots. The pictures will always be taken in the same position, with the patient lying supine on a stretcher, with the photographic template in place (see “treatment area”), with the target area facing the camera that will be at a distance of 60 cm from the patient. The environment will be controlled to maintain optimum light level. The pictures will be stored in files for further analysis using the web-based free-access software ImageJ. Each picture will be identified only with each patient's protocol number and time it was taken (D0—pre-treatment, D7—7 days after treatment; D60 - 60 days after treatment). The ImageJ Software will be used to measure the length of the telangiectasia treated, residual telangiectasias, and hyperpigmented spots. The results obtained in pixels will be transformed by a simple mathematical rule of three by conversion in the ruler of the photographic template. By this mean we will obtain objective measurements of both the disappearance of telangiectasias and of any patches of hyperpigmentation. Personal information and photos will not be published, except for group results and the parts that could not identify the person.

### Treatment (D0)

2.8

After the photographic record of the first visit (D0), all patients will be treated similarly, aiming to eliminate all telangiectasia of the target area. The same physician will perform all the procedures. The treatment technique will be the conventional one, consisting of careful direct puncture of the telangiectasias in order to avoid infiltration of the subcutaneous tissue. The procedure will be conducted until the telangiectasias are undetectable. The maximum volume allowed by puncture will not exceed 0.3 mL. A plastic syringe, luer lock tip, with 3 mL will be used to apply the solution (BD), and the needle will be 13 × 0.4 mm (Terumo - or 27G ^1/2^ inch). The punctures will be occluded with a small cotton ball and a square piece of microporus surgical tape.

All events during the treatment will be recorded in this visit, including the amount of agent used for the disappearance of telangiectasias, possible allergic reactions, and others. Soon after the session, the patient will be invited to answer a questionnaire with questions related to discomfort or pain triggered by the treatment, that was already used in a previous similar study (Fig. 2).^[18]^

**Figure 2 F2:**
[figure not shown]
Assessment form to be filled by the patient after the treatment.

Patients will receive verbal and written instructions on how to proceed with post-treatment care (Fig. 3). All patients will receive a tube of cream containing sodium heparin 0.5% to treat bruises, hematomas, or any phlebitis resulting from the treatment. The medication should be applied for topical use twice daily for 2 weeks.

**Figure 3 F3:**
[figure not shown]
Instructions sheet for patients after the sclerotherapy treatment for telangiectasia.

### Post-treatment (D7)

2.9

Around the seventh day, considering the patient's availability to attend, a new clinical evaluation will be carried out (7 days with a tolerance of ± 4 days after the treatment session; D7). On this visit, the initial results of the treatment will be evaluated, with main focus on minor adverse events such as mild allergies, localized edema, cough, lipothymia, brief scotoma, bruises, and phlebitis, as well as major adverse events such as syncope, DVT, severe allergies, or other major injuries to health. If identified, these events will be recorded in a specific form for this visit. Early phlebitis of the treated vessels can occur with some frequency, and if present will be drained through punctures with a needle (13 gauge × 4.5 BD) and extraction of the thrombus with gentle compression. During this visit, pictures will be taken in the manner described above and the images stored for future analysis.

### Post-treatment (D60)

2.10

After 60 days of treatment, with ± 15-day, the last clinical evaluation will be conducted. This visit is intended to solve issues relating to the efficacy and safety of the treatment, and a new photographic record will be held under the same conditions previously described. In addition, any delayed adverse events will be recorded (such as allergies, edema, respiratory symptoms, syncope, scotoma, suspected DVT, phlebitis, and ulcerations). In case of late phlebitis, treatment will be the same as described for “D7.”

If the patient did not attend any of the visits will be carried out consecutive daily telephone calls to try to rescue the patient and schedule a new visit, provided it remains within the deadline.

To summarize the stages of the study, see flow diagram in Fig. 4 and see the supplemental digital content 3 with Standard Protocol Items: Recommendations for Interventional Trials (SPIRIT).

**Figure 4 F4:**
[figure not shown]
Flowchart of patients in the study.

### Outcomes

2.11

#### Efficacy endpoint

2.11.1

The primary objective (efficacy) will be based on the ability of each treatment to promote the disappearance of treated telangiectasia after 60 days. The analysis will be done by comparing the initial lengths of the telangiectasia before treatment (D0) and the residual telangiectasia after 60 days of treatment (D60), always limiting the comparison to the same patient and same treatment area as previously described. The linear measurement tool of the ImageJ software will measure the length in pixels and transform by a rule of three, through the scale ruler, rendering the results comparable for numerical equivalence in centimeters. Each case will be examined by 2 external evaluators (2 vascular surgeons with experience in the topic), unaware of the treatments conducted, the study therefore being triple-blind. According to the image, the examiners will produce absolute values that will be statistically compared.

For possible conflicting results where very different values are displayed (>10% difference), a meeting will be held between the examiners and a consensus will be established (still blinded to the study treatments). Finally, for statistical purposes, the average of the results obtained for all cases by the 2 examiners will be used.

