#### Secondary outcomes

2.11.3

All the situations that may be indirectly involved with the results in terms of efficacy and safety, among them volume of drug used, number of punctures, skin color, and pain related to the treatment, will be analyzed in the secondary endpoints. Other adverse events as mild allergies, localized or diffuse edema, cough, mild lipothymia, hematomas and phlebitis, besides major adverse events such as syncope, DVT, severe allergies or other major health injuries will also be evaluated, as secondary endpoints.

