### Statistical analysis

2.12

Based on alpha = 0.05, and assuming a standard deviation in the primary endpoint score of 1.5, with 48 participants in each arm, we have >80% power to detect a minimum difference in scores of 0.9. Only 1 extremity will be included per patient and the analysis will be conducted comparing results per patients. It is expected that 10–20% of patients will be lost during follow-up. To promote the most statistically rigorous method, we will use a larger sample size of at least 115 patients. Data will be evaluated either by Student's *t* test or nonparametric Mann–Whitney test (if relevant conditions are not met). Categorical variables (e.g., proportions) will be compared between groups using the χ 2 or Fisher's exact test when necessary. Scores between the groups will be compared with Mann–Whitney test. Multiple comparisons between and within multinomial populations will be analyzed by Goodman association test. All statistical analyzes will be conducted using STATA v11 software (Stata Corp, College Station, TX). All analyses will be performed on an intent-to-treat basis.

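### The between-arm test of telangiectasia length makes no adjustment for the D0 length measured in every patient; it is valid but gives up efficiency and leaves chance baseline imbalance in the estimate

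*Protocol article*

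**What the plan says.** Section 2.11.1 (Efficacy endpoint) rests the primary objective on "comparing the initial lengths of the telangiectasia before treatment (D0) and the residual telangiectasia after 60 days of treatment (D60"), within the same patient and the same treated area. Lengths are read in ImageJ and converted to centimetres, and "the examiners will produce absolute values that will be statistically compared". The two readers' results are averaged.

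Section 2.12 (Statistical analysis) gives the test: Student's t, "or nonparametric Mann–Whitney test (if relevant conditions are not met"). It names no covariate, ANCOVA or regression model, and section 2.3 describes allocation without stratification by D0 extent.

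The sample size is set "Based on alpha = 0.05", "assuming a standard deviation in the primary endpoint score of 1.5", and "with 48 participants in each arm, we have >80% power to detect a minimum difference in scores of 0.9". Section 2.1 gives the same total: "The sample size was statistically estimated as 96 treated limbs". The planning quantity is called a score and has no unit.

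**The concern.** The treated window is the same size for everyone (150 cm², section 2.6), but the length of vessel inside it will differ from patient to patient. A patient who starts with more has more that can remain at D60 and more that can be cleared. A two-sample test on D60 length puts that variation into the error term. A test on change in centimetres subtracts D0 with a fixed weight of one, which over-corrects whenever the true slope is below one: an arm that happens to start with more disease then shows more centimetres cleared at equal efficacy.

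Two things are at stake. One is precision that could be had from data already collected. The other is a chance D0 difference between arms that stays in the one estimate the trial will produce.

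**Working it through.** **Inputs from the document.** Alpha 0.05 (taken as two-sided; not stated), SD 1.5, difference 0.9, 48 per arm (all section 2.12).

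**Assumption.** The D0–D60 correlation r is not given, so 0.3, 0.5 and 0.7 are shown.

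**Step 1: the plan's own figure.** Noncentrality = 0.9 / (1.5 × √(2/48)) = 0.9 / (1.5 × 0.2041) = 2.94. With 94 degrees of freedom, power is 82.9% (83.6% by the normal approximation). The claim of more than 80% reproduces as an unadjusted comparison.

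**Step 2: D60 length adjusted for D0, if 1.5 is the SD of D60 length.** Residual SD = 1.5 × √(1 − r²).

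| r | residual SD | noncentrality | power at 48 per arm |
|---|---|---|---|
| 0.3 | 1.431 | 3.08 | 86.2% |
| 0.5 | 1.299 | 3.39 | 91.9% |
| 0.7 | 1.071 | 4.12 | 98.3% |

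At r = 0.5 the variance falls by 25%, so an unadjusted test would need 48 / 0.75 = 64 per arm for the same precision.

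**Step 3: the other reading, if 1.5 is the SD of the change.** With equal SDs at D0 and D60, ANCOVA variance divided by change-score variance is (1 + r)/2. By the normal approximation, ANCOVA power at 48 per arm is 95.4%, 92.4% and 89.0% for r = 0.3, 0.5 and 0.7, against 83.6% unadjusted. Adjustment gains here too, and most where r is low.

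**Step 4: simulation.** 20,000 trials per setting, normal data, SD 1.5 at both times, 48 per arm:

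| r | t on D60 | t on change | ANCOVA |
|---|---|---|---|
| 0.3 | 82.6% | 69.0% | 85.5% |
| 0.5 | 83.3% | 82.9% | 91.6% |
| 0.7 | 82.8% | 96.4% | 98.2% |

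With no true effect, all three reject in about 5% of trials.

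**Step 5: chance imbalance.** The difference in mean D0 between arms has standard error √(2/48) = 0.204 SD, so its 95% range is ±1.96 × 0.204 = ±0.40 SD. At that edge the unadjusted D60 difference moves by r × 0.40 × 1.5: 0.18, 0.30 or 0.42, which is 20%, 33% or 47% of the 0.9 target. With equal SDs the change score moves the other way, by (1 − r) × 0.40 × 1.5: 0.42, 0.30 or 0.18. Among null trials with imbalance beyond that edge, the unadjusted D60 test rejected in 9.7%, 19.5% and 33.2%; ANCOVA rejected in about 5%.

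**Step 6: scale.** Lengths may be skewed, so a skewed scenario was also simulated. Its inputs are assumptions with no source in the document: lognormal D0 with median 30 cm and log-SD 0.5, mean residual fraction 25% against 15%, 48 per arm. With r about 0.54, Mann–Whitney on D60 reached 85% power against 78% for linear ANCOVA on raw centimetres. Rank-based ANCOVA beat Mann–Whitney in all three variants run: 89% against 85%, 84% against 74%, and 97% against 89%.

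**The case against.** **D0 may already be used.** The phrase about absolute values can be read as describing raw reader output, and the same paragraph compares D0 with D60 within the patient. That is fair, and the text leaves the between-arm quantity open. But a change score still falls short of ANCOVA (Steps 3 to 5). Proportion cleared would weaken the point: in simulated skewed scenarios an unadjusted t test on it beat linear ANCOVA on raw centimetres (for example 85% against 77%). The text, however, speaks of absolute values and names no proportion.

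**The Mann–Whitney fallback may recover the loss.** This stands in part. For skewed lengths it can beat ANCOVA on raw centimetres, so untransformed ANCOVA is not the right remedy in every case. It does not justify omitting D0, since rank-based ANCOVA did better still.

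**The size is not known.** This stands. No r is given, and at r = 0.3 the gain is about 3 percentage points if 1.5 refers to D60 length.

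**Hyperpigmentation.** A reader might extend the point to this outcome, because the article says that "volume of drug used, number of punctures, skin color, and pain related to the treatment, will be analyzed in the secondary endpoints" and skin colour is known before treatment. The document does not support that. Section 2.11.2 already refers hyperpigmentation to pre-treatment telangiectasia length, and section 2.11.3 introduces skin colour as something that may bear on the results. That wording does not exclude its use as a covariate.

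**Conclusion.** The point holds as one of efficiency and of conditional imbalance. The article names the test and leaves out a baseline value that it collects in every patient; this is a choice made in the text and not mere silence left to an analysis plan. Whether D60 length or change is tested, adjustment for D0 improves on it. If 1.5 is the SD of D60 length, power at 48 per arm goes from 83% to about 86%, 92% or 98% for r = 0.3, 0.5 or 0.7. These figures rest on an assumed r, a two-sided alpha and roughly normal data.

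A reader might infer that the planned test is biased, inflates the type I error or leaves the trial underpowered. The document does not support this. Under randomisation the unadjusted test is unbiased over repeated trials, its overall error rate stays near 5%, and the stated power is met. The shifts in Step 5 apply only given a particular imbalance.

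**What to change.** In section 2.12, name D60 residual length as the quantity compared between arms. Make the primary analysis a model of that length on treatment with D0 length as covariate. Prespecify a scale suited to skewed lengths, with a transformed or rank-based ANCOVA if the assumptions on raw centimetres fail. Report the adjusted difference with its 95% confidence interval, and keep the unadjusted t or Mann–Whitney test as a sensitivity analysis.

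This takes one or two sentences and one degree of freedom. D0 length is already measured, so no patients, visits or readings are added, and the sample size need not change.
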